| Related | Abdominal distension, Blood pressure increased, Urticaria, Abnormal sensation in eye, Hyperglycaemia, Duodenitis, Gastritis, Lip dry, Keratoconjunctivitis sicca, Oropharyngeal Pain, Malaise | 1 | 22 |
| Blood urine present,, Reflux oesophagitis, Hypertriglyceridaemia,  Gamma-glutamyltransferase increased | 2 |
| Headache | 3 |

List of adverse events in repeated administration (2)

| Dose | Causal relationship | Events | Number of events | Total |
| --- | --- | --- | --- | --- |
| 900 mg  (At the start n= 9)  * Discontinued during repeated administration | None | Vertigo, Abdominal pain upper, Joint swelling, Chest pain, Alanine aminotransferase increased, Aspartate aminotransferase increased, Blood lactate dehydrogenase increased, Varices oesophageal, Pyrexia, VIth nerve paralysis, Scar,Back pain, Protein urine, Oropharyngeal discomfort, Insomnia, Headache, Nausea | 1 | 23 |
| Nasopharyngitis | 6 |
| Related | Diarrhoea, Chapped lips, Abdominal pain upper, Retinal haemorrhage, Stomach discomfort | 1 | 26 |
| Dysgeusia, Abdominal pain, Protein urine present, Musculoskeletal stiffness | 2 |
| Urinary occult blood positive | 3 |
| Blood pressure increase | 4 |
| Headache | 6 |

Among the 9 subjects who moved on to repeated administration at Level 3, 1 subject was suspended from drug administration and 3 subjects were discontinued from the study due to increased blood pressure. In 1 subject who exhibited blood pressure increase, fundal haemorrhage was observed. However, the subject was placed on observation without requiring medical intervention.

The incidences of events suggesting the presence of effects on renal functions, such as protein urine and urinary occult blood, also increased as compared with Level 1 and Level 2. The numbers of subjects whose protein urine and urinary occult blood shifted to + or more after the start of repeated administration at each level are shown in the table below. Abnormal changes of protein urine and urinary occult blood after the start of repeated administration were also observed in subjects who showed no blood pressure increase, suggesting that NIK-333 affects renal functions.

Frequency of subjects exhibiting a shift to (+) after repeated administration at
each level

|  | Change  Dose | Level of change: From baseline | | | | |
| --- | --- | --- | --- | --- | --- | --- |
| None | 1 grade | 2 grades | 3 grades | 4 grades |

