Note 4: See Table 1, Table 2 and Table 3 at the end of this document for details about the contents of the tests.

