Take body temperature (axillary), blood pressure (systolic/diastolic), pulse rate (dorsal position or sitting position) and body weight at 4-week intervals from the start of study drug administration (within 14 days before the start of administration) until the end of study drug administration, and at the time of follow-up examination.

If the study has been discontinued, body temperature (axillary), blood pressure (systolic/diastolic), pulse rate (dorsal position or sitting position) and body weight will be determined to the extent possible.

[6] Laboratory tests

Collect blood and urine samples and determine the following parameters at 4-week intervals from the start of study drug administration (within 14 days before the start of administration) until the end of study drug administration, and at the time of follow-up examination.

If the study has been discontinued, blood and urine samples will be collected and the following parameters will be determined to the extent possible.

1) Hematology tests: White blood cell count, red blood cell count, hemoglobin level, hematocrit, platelet count

2) Blood biochemistry tests: Total protein, serum albumin, serum bilirubin, total cholesterol, LDL cholesterol, HDL cholesterol, triglyceride, blood glucose, urea nitrogen, Cl, Na, K, Ca, ALP, AST (GOT), ALT (GPT), LDH, -GTP, choline esterase, serum creatinine, A/G ratio, free fatty acid, 2-microglobulin

3) Urinary tests (fresh urine): Qualitative (glucose, protein, urobilinogen, ketone body, occult blood), urinary albumin (converted to creatinine), urinary sediment (red blood cells, white blood cells, epithelial cells, casts, others), 2-microglobulin

[7] Blood pressure parameters

Collect blood and urine samples and determine the following parameters at 48-week intervals from the start of study drug administration until the end of study drug administration. If the systolic blood pressure exceeds 140 mmHg or the diastolic blood pressure exceeds 90 mmHg on two or more successive measurements, blood pressure parameters will be determined at the time of second or subsequent examination. However, determination of creatinine clearance, one of the blood pressure parameters, under increased blood pressure will be conducted to the extent possible.

1) Blood biochemistry tests: Renin activity, aldosterone, cortisol, uric acid, FT3, FT4, TSH, angiotensin II, hANP, BNP, catecholamine, growth hormone, dehydroepiandrosterone sufate (DHEAS)

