2） Urinalyses (accumulated urine): creatinine clearance (if possible)

[8] Bone densitometry

Determine bone density of lumbar vertebrae (L2 to L4) with DXA before the start of study drug administration (period after radical therapy and before administration of the study drug) and at 48-week intervals until the day of the end of study drug administration.

If the study has been discontinued, bone density of lumbar vertebrae will be tested using DXA to the extent possible.

[9] Endoscopy

Conduct endoscopy of the stomach and esophagus before the start of study drug administration (period after radical therapy and before administration of the study drug) and at 48-week intervals until the day of the end of study drug administration.

If the study has been discontinued, endoscopy of the stomach and esophagus will be performed to the extent possible.

[10] ECG

Perform ECGs (12-lead) before the start of study drug administration (period after radical therapy and before administration of the study drug) and at 24-week intervals until the day of the end of study drug administration.

If the study has been discontinued, perform ECGs (12-lead) to the extent possible.

[11] Echocardiography

Perform echocardiography before the start of study drug administration (period after radical therapy and before administration of the study drug) and at 48-week intervals until the day of the end of study drug administration.

If the study has been discontinued, perform echocardiography to the extent possible.

[12] Pulse wave examination

Perform pulse wave examination before the start of study drug administration (period after radical therapy and before administration of the study drug) and at 48-week intervals until the day of the end of study drug administration.

If the study has been discontinued, perform pulse wave examinations to the extent possible.

[13] Fundus examination

Perform fundus examination before the start of study drug administration (period after radical therapy and before administration of the study drug) and at 48-week intervals until the day of the end of study drug administration.

If the study has been discontinued, perform fundus examination to the extent possible.

(2) Adverse events

Adverse events are defined as any unfavorable or unintended signs (including abnormal variations of laboratory test values), symptoms or diseases observed after administration of the study drug, irrespective of the causal relationship with the study drug concerned.

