| Child-Pugh classification | Liver encephalopathy, ascites, serum bilirubin, serum albumin, prothrombin time |
| HCV-RNA | Quantitative |
| HBs antigen | Qualitative |
| HCG tests | Pregnant or not (premenopausal women only) |
| Hematology tests | Platelet count, hemoglobin level |

*: Menopausal status and whether or not being pregnant will be confirmed for female subjects.

Table 2 Examination, observation and evaluation parameters during the study drug administration period (including the day of the start of administration)

| Examination parameters | Examination, observation and evaluation parameters |
| --- | --- |
| Gene expression analysis | Gene expression profile in the liver and peripheral blood |
| Exploratory biomarker | TGF- concentration in plasma (biomarker associated with gene expression) |
| Pharmacokinetics | Drug concentrations in the liver, plasma and urine  (unchanged NIK-333 and NIK-333 lipids form) |
| Abdominal imaging/  diagnosis | Presence or absence of HCC on dynamic CT, US, and MRI images |
| Medical examination | Symptoms*, signs |
| Vital signs, etc. | Body temperature (axillary), blood pressure (systolic/diastolic: dorsal position or sitting position), pulse rate (dorsal position or sitting position), body height#, body weight |
| HCV-RNA | Quantitative (including genotype analysis#) |
| HCG tests | Pregnant or not (premenopausal women only) |
| Hematology tests | White blood cell count, red blood cell count, hemoglobin level, hematocrit, platelet count |
| Blood biochemistry tests | Total protein, albumin, bilirubin, total cholesterol, LDL cholesterol, HDL cholesterol, triglyceride, blood glucose, urea nitrogen, Cl, Na, K, Ca, ALP, AST, ALT, LDH, -GTP, choline esterase, serum creatinine, A/G ratio, free fatty acid, 2-microglobulin |
| Blood pressure parameters | Blood biochemistry tests: Renin activity, aldosterone, cortisol, uric acid, FT3, FT4, TSH, angiotensin II, hANP, BNP, catecholamine, growth hormone, dehydroepiandrosterone sufate (DHEAS)  Urinary tests (accumulated urine): creatinine clearance |
| Tumor markers | AFP，AFP-L3，PIVKA-II |
| Fibrosis marker | Hyaluronic acid |
| Urinary tests (fresh urine) | Qualitative (glucose, protein, urobilinogen, ketone body, occult blood)  urinary albumin (converted to creatinine), urinary sediments (red blood  cells, white blood cells, epithelial cells, columnar cells, others)  2-microglobulin |
| Bone densitometry (DXA) | Bone density of lumbar vertebrae (L2 to L4) |

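### Urinary albumin is converted to creatinine, but no conversion is stated for the microglobulin in the same untimed urine, so its values mix excretion with urine dilution

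*Protocol*

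**What the plan says.** Section 7.5(1)[6]3) of the protocol lists the fresh-urine tests done every 4 weeks and at follow-up. After the qualitative items it gives "urinary albumin (converted to creatinine), urinary sediment (red blood cells, white blood cells, epithelial cells, casts, others", and then a microglobulin. Table 2 (treatment period) and Table 3 (follow-up) repeat the panel: "urinary albumin (converted to creatinine), urinary sediments (red blood" and the remaining sediment items, ending with "2-microglobulin" (the Greek prefix is lost in the text available to me). In all three places the creatinine conversion is attached to albumin only.

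Timed urine is also collected (section 4.9), but among the safety tests it serves one purpose: "Urinalyses (accumulated urine): creatinine clearance (if possible".

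Section 12.3 asks for lists, time-course charts and summary statistics of the laboratory values. It names no test, threshold or decision rule.

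The renal background is explicit. Section 2.3 reads the phase I urine findings as "suggesting that NIK-333 affects renal functions", and the Step II rationale in section 4.4(3) names the urinary system as an object of the long-term safety examination.

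On the sediment, 7.5 names casts, while Tables 2 and 3 read "epithelial cells, columnar cells, others". Note 4 to the schedule says: "See Table 1, Table 2 and Table 3 at the end of this document for details about the contents of the tests".

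**The concern.** The protocol accepts that one quantitative protein in spot urine needs correcting for dilution. It states no correction for the other one in the same specimen and gives no reason for the difference. At constant excretion, halving the urine water doubles an uncorrected concentration with no change in the kidney.

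Step II has a single dose, no concurrent comparison group and at most 12 subjects, so each subject's change from baseline is the evidence. A value that moves with urine concentration can blur a real change in excretion or look like one when there is none.

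**Working it through.** **Text comparison.** The protocol gives no figure to reproduce, so the first check is of wording.

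| Place | Albumin | Microglobulin | Fourth sediment item |
| --- | --- | --- | --- |
| 7.5(1)[6]3) | converted to creatinine | no conversion stated | casts |
| Table 2 | converted to creatinine | no conversion stated | columnar cells |
| Table 3 | converted to creatinine | no conversion stated | columnar cells |

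On the conversion the three places agree, so this is a measure that is poorly fixed, not a contradiction. On the sediment item they differ.

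**Number of tests.** The schedule has one fresh-urine test at the start, 24 on treatment (Weeks 4 to 96 every 4 weeks: 96/4 = 24) and one at follow-up, 26 in all. Urine creatinine is needed at each of them for albumin.

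**Size of the dilution noise.** Assumption, not in the protocol: the within-subject CV of spot-urine creatinine, standing in for dilution, is 30% to 60%, log-normal and independent between visits.

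- Log-SD = sqrt(ln(1 + CV²)): sqrt(ln 1.09) = 0.294 and sqrt(ln 1.36) = 0.555.
- One visit against baseline: SD = sqrt(2) × log-SD = 0.415 to 0.784. The 95% fold range is exp(1.96 × SD) = 2.26 to 4.65, up or down.
- Chance of an apparent rise of twofold or more in one such comparison: P(Z ≥ ln 2 / SD) = 4.7% to 18.8%.
- Mean of 24 on-treatment visits against the one baseline: SD = log-SD × sqrt(1 + 1/24) = 0.300 to 0.566. The 95% fold range is 1.8 to 3.0.
- Margin on the mean change in 12 subjects, exp(t(0.975; 11) × SD/sqrt(12)): ×1.30 to ×1.65 for one visit, and about ×1.21 to ×1.43 for the 24-visit mean.

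Averaging the on-treatment visits helps only so far, because the single baseline value keeps its full dilution error: exp(1.96 × 0.294) = 1.8 and exp(1.96 × 0.555) = 3.0.

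**Share of the total variation.** The figures above are for dilution alone. Let CVd be the CV from dilution and CVe the CV of creatinine-corrected excretion, taken as independent. The dilution share of the log-variance is ln(1 + CVd²) / [ln(1 + CVd²) + ln(1 + CVe²)]. Both CVs are assumed.

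| CVd | CVe | Dilution share | 95% fold range, one visit against another: uncorrected → corrected |
| --- | --- | --- | --- |
| 0.3 | 1.0 | 11% | 11.6 → 10.1 |
| 0.5 | 1.0 | 24% | 14.2 → 10.1 |
| 0.5 | 0.5 | 50% | 6.4 → 3.7 |
| 0.5 | 0.3 | 72% | 4.7 → 2.3 |
| 0.7 | 0.2 | 91% | 6.3 → 1.7 |

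The share passes one half only when CVd exceeds CVe. Under this model the corrected range is always the narrower one, but the gain runs from small to large.

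**The case against.** The strongest reply is that the protocol lists an assay and does not prescribe a raw-concentration analysis. A ratio is a derived variable that a statistical analysis plan could define, and since urine creatinine is measured anyway, nothing is lost for good. The analysis is descriptive. The phase I signals were urinary protein and occult blood, and these are followed by several other items: qualitative tests, creatinine-corrected albumin, sediment, serum creatinine, urea nitrogen and creatinine clearance. There are also 24 on-treatment visits, so a single-visit range overstates the noise in a time course.

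Much of this stands, and it limits the consequence: the microglobulin is one supporting item, and repeated visits reduce the range as shown. It does not remove the point. The protocol itself fixes how albumin is expressed and leaves the second protein in the same specimen without a dilution correction. Section 12.3, followed as written, would then chart and summarise that value.

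Three stronger readings may tempt a reader, and the documents do not support them.

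- *The microglobulin mostly follows urine concentration.* The protocol gives no variability figures, and the share runs from 11% to 91% over the assumed CVs.
- *Fractional excretion should be reported as well.* That requires the serum and urine microglobulin to be the same analyte, which cannot be confirmed here because both prefixes are lost in the text.
- *Casts are no longer examined.* Section 7.5 names them, the tables keep an open category for other findings, and Note 4 does not say that the tables override 7.5. A translation slip is plausible, though the documents cannot settle it.

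**Conclusion.** The point holds as a weakness in how one safety measure is specified. With no stated conversion, the urinary microglobulin mixes excretion with dilution, in a trial that names the urinary system as a Step II safety target. Under the assumed CV of 30% to 60%, dilution alone gives one subject a 95% range of about 2.3- to 4.7-fold for one visit against baseline, and about 1.8- to 3.0-fold for the 24-visit mean. These figures rest on the assumed CV, on independent visits and on creatinine tracking dilution. What part of the marker's total variation this represents is unknown. The effect on the trial's conclusions is modest because the analysis is descriptive, but the improvement costs almost nothing. The sediment wording is a minor editorial matter.

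**What to change.** - In section 7.5(1)[6]3) and in Tables 2 and 3, write: *urinary albumin and urinary microglobulin (both converted to creatinine)*.
- Summarise each subject's change from baseline in the microglobulin-to-creatinine ratio on the log scale, and keep the raw value in the listings.
- Optionally add fractional excretion, (urine microglobulin × serum creatinine) / (serum microglobulin × urine creatinine), but only after confirming that the serum and urine assays measure the same microglobulin.
- Editorially, reconcile columnar cells in Tables 2 and 3 with casts in 7.5.

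The cost is a wording change and one derived variable. None of the 26 scheduled fresh-urine tests needs a new sample or assay for the ratio.
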